## Abstract

**Background:**

Acute kidney injury is a common and devastating complication of critical illness, for which renal replacement therapy is frequently needed to manage severe cases. While a recent systematic review suggested that “earlier” initiation of renal replacement therapy improves survival, completed trials are limited due to small size, single-centre status, and use of variable definitions to define “early” renal replacement therapy initiation.

**Methods/design:**

This is an open-label pilot randomized controlled trial. One hundred critically ill patients with severe acute kidney injury will be randomly allocated 1:1 to receive “accelerated” initiation of renal replacement therapy or “standard” initiation at 12 centers across Canada. In the accelerated arm, participants will have a venous catheter placed and renal replacement therapy will be initiated within 12 hours of fulfilling eligibility. In the standard initiation arm, participants will be monitored over 7 days to identify indications for renal replacement therapy. For participants in the standard arm with persistent acute kidney injury, defined as a serum creatinine not declining >50% from the value at the time of eligibility, the initiation of RRT will be discouraged unless one or more of the following criteria are fulfilled: serum potassium ≥6.0 mmol/L; serum bicarbonate ≤10 mmol/L; severe respiratory failure (PaO_2_/FiO_2_<200) or persisting acute kidney injury for ≥72 hours after fulfilling eligibility. The inclusion criteria are designed to identify a population of critically ill adults with severe acute kidney injury who are likely to need renal replacement therapy during their hospitalization, but not immediately. The primary outcome is protocol adherence (>90%). Secondary outcomes include measures of feasibility (proportion of eligible patients enrolled in the trial, proportion of enrolled patients followed to 90 days for assessment of vital status and the need for renal replacement therapy) and safety (occurrence of adverse events).

**Discussion:**

The optimal timing of renal replacement therapy initiation in patients with severe acute kidney injury remains uncertain, representing an important knowledge gap and a priority for high-quality research. This pilot trial is necessary to establish protocol feasibility, confirm the safety of participants and obtain estimated events rates for design of a large definitive trial.

**Trial registration number:**

NCT01557361

## Background

Acute kidney injury (AKI) is a common complication in critically ill patients. Among those with severe AKI, 50 to 70% will receive renal replacement therapy (RRT) [1]. RRT increases the complexity and costs of care and is associated with death, with case-fatality rates commonly exceeding 60% [1,2], and dialysis dependence among survivors [2-4].

Methods of providing RRT to patients in the ICU vary widely, reflecting uncertainty surrounding many aspects of this therapy [5,6]. It is generally understood that life-threatening AKI complications, such as severe hyperkalemia, profound acidosis and fluid overload resulting in respiratory failure, are absolute indications for RRT. However, outside of these indications, the optimal time to start RRT in critically ill patients with severe AKI remains unknown. Early initiation of RRT has the intuitive appeal of avoiding life-threatening AKI complications; however, RRT is not without complications and costs [7,8], and in the setting of chronic dialysis for end-stage renal disease, no evidence of benefit was found with earlier start times [9].

We recently performed a systematic review of the effect of RRT timing on mortality in adult critically ill patients, and included 15 studies published between 1999 and 2010 [10]. In a pooled analysis limited by low methodological quality of the included studies and important statistical heterogeneity, early (versus later) initiation of RRT was associated with a significantly reduced odds of death (odds ratio 0.45, 95% CI 0.28, 0.72). The largest published randomized controlled trial (RCT) (n=106) of RRT timing found no difference in mortality; however, it was underpowered to detect a clinically implausible absolute difference in mortality of less than 40% [11]. For comparison, the large multi-cente rtrial, Randomized Evaluation of Normal versus Augmented Level Renal Replacement Therapy (RENAL),enrolled 1,508 critically ill patients with severe AKI and was powered to detect a minimal difference in 90-day mortality of 7.5% [12].

Given the limitations of published studies, a large and methodologically rigorous RCT is needed to evaluate the impact on survival and renal recovery of earlier versus current usual criteria for RRT initiation in critically ill adults with severe AKI. This question has also been identified as a top research priority by the Acute Kidney Injury Network [13] and endorsed by intensivists and nephrologists [14].

Our objective is to conduct a Canadian multi-centerRCT in critically ill patients with severe AKI, comparing the effect of accelerated versus standard RRT initiation on 90-day mortality and dialysis dependence among 90-day survivors. To support this trial, we propose to perform a pilot trial to evaluate protocol adherence, estimate recruitment rates, confirm that meaningful separation in the timing of RRT between treatment arms can be achieved, and evaluate safety.

## Methods/design

### Design

The design is an open-label, multi-center, pilot, randomized controlled trial of accelerated versus standard initiation of RRT initiation in critically ill patients with severe AKI.

### Setting

The setting is the ICU at 12 academic hospitals across Canada. Site investigators are listed in Additional file 1.

### Population

Eligible participants will fulfill all inclusion and no exclusion criteria (see Additional file 2).

### Inclusion criteria

The inclusion criteria are designed to identify a population of critically ill adults with severe AKI who have an increased likelihood of receiving RRT during their hospitalization, but who do not have urgent indications for the initiation of RRT at the time of fulfilling eligibility criteria. All six criteria must be fulfilled at the time of screening:

1. Age ≥18 years.

2. Admission to an ICU.

3. Evidence of kidney dysfunction (serum creatinine above the upper threshold of normal for commercially available laboratory assays (women ≥100 μmol/L; men ≥130 μmol/L)

4. Evidence of severe AKI based on at least two of the following three criteria:

i. A 2-fold increase in serum creatinine during hospitalization or from a known pre-hospitalization baseline with current creatinine no less than 25 μmol/L below peak (consistent with the Risk, Injury, Failure, Loss, End-stage renal failure (RIFLE) INJURY category of AKI);

i. Oliguria as defined by urine output <6 mL/kg over the preceding 12 hours (consistent with RIFLE category of AKI);

i. If only one of two above criteria for severe AKI are met and all other eligibility criteria are fulfilled, a whole-blood Cardiorenal Neutrophil Gelatinase-Associated Lipocalin™ (NGAL)(Alere Inc., San Diego, CA, USA) ≥400 ng/mL.

5. Likelihood that an absolute indication for RRT will not arise in the subsequent 24 hours based on the most recent blood laboratory values:

i. Serum potassium ≤5.5 mmol/L, and

i. Serum bicarbonate ≥15 mmol/L.

6. Central venous pressure ≥8 mmHg. The rationale for this criterion is to ensure adequate volume resuscitation and mitigate enrollment of patients with hypovolemia or AKI that will readily improve with fluid administration.

### NGAL testing for eligibility

NGAL is a novel biomarker that is upregulated early in the course of AKI [15]. Whole blood (0.25 to 0.50 mL) will be tested using a fluorescence immunoassay that operates on the Triage™ platform (Alere Inc.) and yields quantitative results within 15 to 20 minutes. NGAL may detect AKI prior to excursions in the serum creatinine [16,17] and has been found useful for discriminating between patients whose elevated serum creatinine values are due to established acute kidney damage (that is, the target population for this trial) compared to chronic kidney disease or uncomplicated volume contraction [18]. A recent meta-analysis also found that plasma NGAL concentrations predict worsening AKI and the receipt of RRT with an estimated area under the receiver operator curve of 0.78 [19]. We chose a cutoff value for NGAL of 400 ng/mL based on data from recently published studies [20,21] which found the operating characteristics for a serum NGAL of 417 ng/mL for predicting the need for RRT (that is, development of RIFLE-Failure AKI) to be as follows: sensitivity 0.70; specificity 0.90; positive predictive value 0.40; and negative predictive value 0.97. The high negative predictive value identifies this threshold as a specific predictor for subsequently receiving RRT [20,21].

### Exclusion criteria

1. Lack of commitment to ongoing life support, including RRT.

2. Presence of a drug overdose that necessitates initiation of RRT.

3. Any RRT within the previous 2 months.

4. Presence or clinical suspicion of renal obstruction, rapidly progressive glomerulonephritis, vasculitis, or acute interstitial nephritis.

5. Known pre-hospitalization advanced chronic kidney disease, defined by an estimated glomerular filtration rate <30 mL/minute/1.73 m^2^, or chronic RRT.

6. Kidney transplant within the past 365 days.

7. Time since first doubling of serum creatinine has exceeded 48 hours.

8. Clinician(s) caring for patient believe(s) that immediate RRT is absolutely mandated.

9. Clinician(s) caring for patient believe(s) that deferral of RRT initiation is mandated.

10. Patient or substitute decision maker is unable to provide consent within 12 hours of determination of study eligibility.

### Eligible, non-randomized patients

Eligible non-randomized patients will be those who meet all inclusion criteria but are not included in the trial for the following reasons:

1. A doubling of serum creatinine that has exceeded 48 hours at the time of screening (exclusion 7);

2. Clinician(s) belief that either immediate RRT is absolutely mandated (exclusion 8) or deferral of RRT initiation (exclusion 9) is absolutely mandated; or

3. Refusal of consent or inability to obtain consent within 12 hours of patient meeting eligibility criteria (exclusion 10).

We will document reasons leading to non-inclusion of these otherwise eligible patients. For these patients, we will collect data on kidney function at baseline and at the time of eligibility, severity of illness at the time of eligibility, receipt of RRT in hospital and need for RRT at hospital discharge, and vital status at ICU and hospital discharge. The collection of these data will enable comparisons with randomized patients to assess threats to the generalizability of the trial results.

### Screening process

Research coordinators will screen patients in each study ICU for eligibility twice each weekday, in the morning and afternoon. Given the dynamic nature of the inclusion criteria, individuals who are not initially eligible for the trial will be re-screened each day. Research coordinators will discuss all patients who meet inclusion criteria, without an exclusion criterion, with the attending intensivist and, if applicable, the attending nephrologist.

### Ethics and consent

The Health Research Ethics Boards (HREB) at the University of Alberta (Edmonton) and St. Michael’s Hospital (Toronto), along with those at each participating site, reviewed and approved the study (see Additional file 3). Research coordinators will approach eligible patients or their substitute decision maker (SDM), in the event of patient incapacity, for informed consent (see Additional file 4). If the SDM provides consent but the patient becomes capable prior to the end of the follow-up period, the research coordinator will seek consent directly from the patient, who will have the option of withdrawing from the study. If an SDM is contactable by telephone but is not able to come in person to sign the consent form, steps will be taken to obtain telephone consent.

At four sites where this study has Research Ethics Board (REB) approval, patients who are eligible but incapable of providing consent and for whom an SDM is not available may be randomized through a process of deferred consent (see Additional file 5). In this circumstance, the research coordinator will endeavor to locate an SDM after patient enrollment, and ask the SDM to affirm or withdraw consent for the patient’s participation. In addition, once the participant regains capacity, he/she will be asked to affirm or withdraw consent for the trial.

### Co-enrollment

Patients recruited to the study, STtandard versus Accelerated initiation of Renal Replacement Therapy in Acute Kidney Injury (STARRT-AKI), may also be enrolled in other studies provided that the steering committee has reviewed the protocol and determined that there is no interference with the timing of RRT initiation mandated by the STARRT-AKI protocol. Prior survey findings have shown clinical researchers’ support for trial co-enrollment of critically ill patients [22].

### Randomization process

Participants will be randomly allocated in a ratio of 1:1, stratified by study center using variable block sizes undisclosed to site study personnel, to accelerated or standard initiation of RRT. The study statistician at the methods centre (Applied Health Research Centre (AHRC), St. Michael’s Hospital, Toronto, Canada) will generate the random allocation sequence using computer software. Randomization information for each site will be contained in locally held sequentially numbered, opaque, sealed envelopes. Envelopes are to be opened in numeric sequence.

### Interventions

Accelerated RRT initiation (experimental arm):a catheter will be placed by the treating ICU or Nephrology team and RRT initiated as soon as possible, and within 12 hours of eligibility. This 12-hour window includes the time needed to obtain consent.

Standard RRT initiation (control arm):the study team will follow patients for 7 days to identify potential indications for RRT. For patients with persistent AKI (serum creatinine has not declined by more than 50% from value at time of eligibility), the protocol discourages RRT initiation unless one or more of the following criteria are met:

1. Serum potassium ≥6.0 mmol/L, or

2. Serum bicarbonate ≤10 mmol/L, or

3. Severe respiratory failure, defined as arterial partial pressure of oxygen(PaO_2_)/inspired oxygen fraction(FiO_2_)<200 and bilateral infiltrates on the chest radiograph, or

4. Persistent AKI (as defined above) 72 hours after eligibility.

Notwithstanding these recommendations, RRT in the control arm may be commenced at anytime, provided >12 hours have elapsed since the patient met eligibility criteria, at the discretion of the attending physician(s). This will not be considered a protocol deviation. If this occurs, the physician will be asked to specify the primary reason for initiating RRT on that day. If RRT is initiated within 12 hours of eligibility, the clinician will also be asked to provide primary reason(s) for this protocol violation.

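### For standard-arm patients who enter with creatinine at or below twice baseline, full recovery still counts as persistent AKI, so the 72-hour criterion does not test persistence in this subset

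*Protocol article*

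**What the plan says.** The protocol article defines persistent AKI twice, in matching terms. The Abstract (Methods/design) has it "defined as a serum creatinine not declining >50% from the value at the time of eligibility". The Interventions section, under standard initiation, has it as "serum creatinine has not declined by more than 50% from value at time of eligibility". In both places the reference is the eligibility value, not the baseline, and the inequality is strict.

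For standard-arm patients with persistent AKI, "the protocol discourages RRT initiation unless one or more of the following criteria are met". The fourth criterion on that list is "Persistent AKI (as defined above) 72 hours after eligibility".

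Entry is governed by the Inclusion criteria section. Criterion 4 asks for "Evidence of severe AKI based on at least two of the following three criteria":

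- the creatinine criterion, "A 2-fold increase in serum creatinine during hospitalization or from a known pre-hospitalization baseline", "with current creatinine no less than 25 μmol/L below peak";
- oliguria over 12 hours;
- whole-blood NGAL of at least 400 ng/mL, used when only one of the other two is met.

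Criterion 3 adds an absolute creatinine floor ("women ≥100 μmol/L; men ≥130 μmol/L"). No upper limit on the rise is stated. Exclusion 7 limits the time since first doubling to 48 hours, not the size of the rise.

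**The concern.** The persistence rule measures recovery as a percentage fall from the eligibility value, and the entry rule allows that value to be no more than twice baseline. For those patients, coming all the way back to baseline is not a large enough fall to leave the persistent category. The fourth standard-arm criterion is the only one of the four meant to ask whether the kidney injury has lasted. In this subset it can be met simply because 72 hours have passed.

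Two things are at stake. First, the discouragement of RRT lapses at 72 hours for a patient whose creatinine has recovered. Second, the Primary and secondary outcomes section says that indications for standard-arm starts will be recorded. A start under this criterion could be recorded as persistent AKI whether or not the injury had persisted, and the definitive trial would be planned from that record.

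**Working it through.** The plan gives no figure that depends on this definition, so there is nothing of its own to reproduce. The check is whether the entry rule and the persistence rule fit together.

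**Inputs.** The persistence threshold is a fall of more than 50% from the eligibility value (Interventions; Abstract). Entry is by inclusion criteria 3 and 4. I read the creatinine criterion as requiring that the doubling was reached at peak and that the current value is not more than 25 μmol/L under that peak. The baselines in step 2 are assumptions, because the article gives none.

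**Step 1: fall at full recovery.** Let R = creatinine at eligibility / baseline. Full return to baseline is a fall of 1 − 1/R. The condition 1 − 1/R > 0.5 requires R > 2. The level that ends persistent status is anything below (R/2) × baseline.

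| R at entry | Fall at full return | Status at baseline | Must fall below |
|---|---|---|---|
| 1.5 | 33.3% | persistent | 0.75 × baseline |
| 1.75 | 42.9% | persistent | 0.875 × baseline |
| 2.0 | 50.0% | persistent | 1.00 × baseline |
| 2.1 | 52.4% | not persistent | 1.05 × baseline |
| 2.5 | 60.0% | not persistent | 1.25 × baseline |
| 3.0 | 66.7% | not persistent | 1.50 × baseline |

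**Step 2: does the entry rule admit R of 2 or less?** It does, by three routes.

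- *Exactly a 2-fold rise.* R = 2, and full recovery is a fall of exactly 50%, which is not more than 50%.
- *Below a just-doubled peak.* With peak 2 × baseline and the current value 25 μmol/L lower, R = (2 × baseline − 25) / baseline:

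| Assumed baseline (μmol/L) | Peak | Entry value | R | Fall at full return |
|---|---|---|---|---|
| 65 | 130 | 105 | 1.62 | 38.1% |
| 80 | 160 | 135 | 1.69 | 40.7% |
| 100 | 200 | 175 | 1.75 | 42.9% |
| 130 | 260 | 235 | 1.81 | 44.7% |

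  All four entry values clear the creatinine floor, the first of them for women only. With a 2.5-fold peak and the same baselines, the falls are 52.7% to 56.7%, so those patients do leave the category.
- *Oliguria plus NGAL.* Two of three criteria suffice, so no doubling is needed. R can be anywhere that the creatinine floor and the other criteria allow, including well under 2.

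**Step 3: patients with R above 2.** They leave the persistent category at or before full return to baseline, so the mismatch does not touch them at full recovery.

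**Step 4: where the definition is used.** It appears in the standard-arm recommendations only. The primary outcome is set by RRT starting before or after 12 hours from eligibility. Separation between arms is measured by start times. Neither calculation takes persistence as an input.

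**The case against.** The strongest reply has four parts.

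- *Two-fold is a floor.* It is the minimum for one of three entry criteria, with no maximum. Up to 48 hours may pass after first doubling, a second criterion must also be met, and screening runs on weekdays only, so creatinine may well have risen past a doubling by entry. This stands. A reader might infer that patients generally enter at about a doubling or less and that the fourth criterion is mostly a clock. The article gives no distribution of entry ratios and does not support that.
- *The criterion requires nothing.* Meeting it only ends a discouragement, and physicians may start RRT in the control arm at their discretion once 12 hours have passed, without a deviation. This also stands. A reader might infer that recovered patients would be dialysed because of the wording, but the document does not show that.
- *The main results do not use the definition.* This stands, as step 4 shows. A reader might infer that protocol adherence or the measured separation in timing is compromised; neither is calculated from this label.
- *Entry and persistence are different quantities, and the eligibility value exists for every patient while a baseline may not.* This explains the choice of reference but does not rescue the result. A rule that calls a patient back at baseline persistent does not do what its name says, whatever reason there was for the reference value.

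One might also call partial recovery at ratios between 2 and 3 misclassified. How much improvement should end persistence is a clinical judgement, and the arithmetic does not settle it.

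**Conclusion.** The point holds for a defined subset: standard-arm patients whose eligibility creatinine is at or below twice baseline. For them, full recovery is a fall of 50% or less, the persistent label cannot be shed by returning to baseline, and the fourth criterion works as a 72-hour clock. This is a stated rule giving a wrong classification, not a detail left to another document.

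The size of the subset cannot be computed; it may be small or large. The effect is confined to when the discouragement of RRT lapses and to the label in the record of indications. The finding rests on the reading of the 25 μmol/L allowance given above and on taking baseline to mean the reference value for the doubling. The exact-doubling and oliguria-plus-NGAL routes do not depend on the allowance. It is worth correcting, but it ranks below must-fix.

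**What to change.** 1. The sponsor should reconcile the persistence definition in the Abstract and Interventions with inclusion criterion 4. The clinical threshold and its reference value are for the steering committee; none is proposed here.
2. In the report of indications for standard-arm starts, tabulate starts under the fourth criterion by creatinine at RRT start, relative to baseline where known and relative to the eligibility value. Starts during recovery can then be told apart from starts with unresolved injury, whatever definition is kept.

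The cost is a wording amendment and one derived variable built on routine blood work that the protocol already documents. The table can also cover patients enrolled before any amendment, which matters because recruitment is active. Patients without a known baseline, who may include some who entered on oliguria plus NGAL, would be shown separately. The primary outcome and the sample size do not change.

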### Renal replacement therapy delivery

Other than the study intervention (that is, differential timing of RRT initiation), all RRT delivered to patients in both treatment arms will follow current clinical practice guidelines [23]. The three commonly used RRT modalities may be used in this study: intermittent hemodialysis (IHD), sustained low efficiency dialysis (SLED), and continuous renal replacement therapy (CRRT). These are summarized in Table 1. The initial RRT modality will be guided by hemodynamic status at the time the patient is ready to start RRT using the cardiovascular component of the Sequential Organ Failure Assessment score (SOFA_CV_) [24]. Following the initiation of RRT, modality switches will be guided by the patient’s hemodynamic profile, as done in a recent large trial [25].

**Table 1 T1:** Delivery of renal replacement therapy in the trial

	**Intermittent hemodialysis**	**Sustained low-efficiency dialysis**	**Continuous renal replacement therapy**
**Patient hemodynamic profile**	Off all vasopressors and inotropes (SOFA_cv_ <2)	Receiving any dose of vasopressor or inotrope (SOFA_cv_ ≥2)	Receiving any dose of vasopressor or inotrope (SOFA_cv_ ≥2)
**Minimum session duration (hrs)**	3	8	24
**Minimum frequency**	3 times/week	3 times/week	NA
**Blood flow target (mL/min)**	200 to 400	200 to 300	100 to 250
**Dialysate flow (mL/min)**	500 to 800	200 to 400	NA
**Total effluent (mL/kg/hr)**	NA	NA	≥25
**Anticoagulation options**	Heparin	Heparin	Heparin
	None	None	None
			Regional citrate anticoagulation
**Fluid removal rate**	To be determined by the nephrologist and/or critical care physician		

This table outlines guidelines for renal replacement therapy prescription by modality for randomized participants. NA, not applicable; SOFA_cv_, cardiovascular component of the Sequential Organ Failure Assessment score [22].

